## Discussion

Reducing the burden of T2D requires novel approaches to improving glycaemic management, particularly for indigenous populations who continue to experience suboptimal glycaemic control and inequities in diabetes-related outcomes. Real-time CGM may offer advances in glycaemic management in T2D without increasing the burden of disease. However, a lack of funded CGM in New Zealand and most locations worldwide continues to limit wide-spread and equitable use of CGM, and inadequate glucose data via subsided SMBG remains a major barrier to improving glycaemic outcomes. Alongside these issues are clinician and health-care system mediators of clinical inertia in diabetes management, such as insufficient time and knowledge deficits in non-specialist settings (e.g., primary care) [41].

A strength of our study design is the model of care provision alongside available glucose testing modalities. To our knowledge, this is the first RCT study investigating the use of rtCGM alongside supported specialist care with a focus on participant self-titration of insulin. Previous studies reporting improvements in glycaemic control using CGM have simultaneously observed only modest adjustments to glucose-lowering therapies in both CGM and control groups [25–27, 42]. Participants in these studies accessed care from their usual care providers during the trial phase. Type 2 diabetes is largely managed in primary care in New Zealand, and while heavily subsidised, the costs associated with visiting a primary care clinician remains a barrier to accessing diabetes care [43, 44]. Furthermore, diabetes specialists may be less prone to clinical inertia than primary care clinicians [45], particularly when specialist care adheres to clinical guidelines [46]. Our study design includes equitable, face-to-face and remote access to prescribing DNS for all study participants, with endocrinologist support for DNS as required. Prescribing DNS will assist participants to make changes to their lifestyle and medication regimens to reduce cardiovascular risk. Prescribing DNS will also support participants in both arms of the trial to self-titrate insulin doses between scheduled study review points. This self-titration education will follow an insulin titration guideline (Appendix) to reduce clinician-mediated inertia and bias in regimen changes between study groups. Bias will also be reduced by optimising non-insulin glucose lowering therapies in the run-in phase before participant randomisation.

A further strength of our study design is the continuous and extensive use of rtCGM. Evidence from other studies using CGM in T2D suggests that the length of CGM system use influences glycaemic outcomes. RCT data from studies by Vigersky et al. [26] and Ernhardt et al. [27] showed that participants who used rtCGM for ≥48 days had greater reductions in Hba1c than those who used rtCGM for <48 days (14 mmol/mol/1.3% versus 9 mmol/mol/0.8% [26] and 13 mmol/mol/1.2% versus 7 mmol/mol/0.6% [27]). Our participants will use rtCGM continuously for 12–24 weeks according to randomisation at baseline. As such, with long duration of rtCGM use alongside supported specialist care and participant self-titration of insulin, we expect glycaemic reductions in this group to be greater than previously reported in rtCGM studies of people with T2D.

We also aim to address other deficits in literature including a paucity of qualitative data from indigenous people with T2D using technology, the effect of rtCGM use on dietary and sleep behaviours and cost-benefit analysis of technology use in high-risk indigenous populations with T2D.

The 2GO-CGM trial is likely to afford participants immediate and long-term benefits. We expect that rtCGM use will be well tolerated, and result in a cost-effective increase in TIR, and decrease in hyperglycaemia, without corresponding increase in hypoglycaemia. Our novel, integrated, remote model of care utilising prescribing DNS with endocrinologist support is likely to be effective in improving glycaemic control and cardiovascular risk in both the rtCGM and SMBG groups, as well as offer a transferable solution to real-world clinical care in the face of increasing challenges in workforce shortage and accessibility of care for people with diabetes. As such, we expect the 2GO-CGM study will provide robust evidence-based and scalable solutions for improving care for high-risk Māori and non-Māori with T2D in New Zealand and worldwide.

## Appendix: Insulin titration management algorithm

Sourced from the New Zealand Society for the Study of Diabetes national guidelines on 9th January 2023 available at www.nzssd.org.nz

### For participants on basal insulin only

- Participants in the control group will monitor their glucose levels before meals and bed, and if symptomatic of hypoglycaemia or hyperglycaemia
- If 3 consecutive fasting glucose levels >7 mmol/L then increase dose of basal insulin by 10% or 2 units (i.e. can increase dose every 3 days if monitoring available)
- Stop uptitration of basal insulin if any of the following occurs:
  - Glucose levels <4 mmol/L at any time of day
  - Fasting glucose level < 7 mmol/L
  - Doses of basal insulin reach 0.5 units/kg/day
- At next study visit, start prandial insulin if glucose levels at any time of day consistently >10 mmol/L. The choice of prandial insulin is a shared decision with the participant based on glucose monitoring, participant factors (e.g., timing of meals, variability of diet, daily routine, comfort/ability to inject and monitor glucose levels etc.) and preference. Options include:
- Addition of bolus insulin at largest meal (basal plus)
  - Start rapid-acting insulin at 4 units or 10% of basal dose at largest meal and titrate as below
- Addition of bolus insulin at all main meals (basal bolus)
  - Start rapid-acting insulin at 4 units or 10% of basal dose at all main meals and titrate as below
- Premixed insulin with largest meal (if predominantly one meal per day)
  - Convert daily dose of basal insulin to premixed insulin before largest meal and titrate as below
- Premixed insulin with breakfast and dinner
  - Convert daily dose of basal insulin to premixed insulin with half the dose pre-breakfast and half pre-dinner. Consider a different ratio if one meal larger than the other (e.g., two thirds/one third) and/or the addition of rapid acting insulin at lunch and titrate as below

### For participants on basal plus regimen

- In addition to the above monitoring, participants in the control group should also check their glucose levels two hours after their largest meal (i.e., 2 hours after bolus insulin administered)
- If 2-hour post-meal glucose level > 3 mmol/L than pre-meal glucose level on 3 consecutive occasions then increase dose of rapid acting insulin by 2 units (i.e., can increase dose every 3 days if monitoring available)
- Stop uptitration of rapid acting insulin if any of the following occurs:
  - Glucose levels <4 mmol/L at any time of day
  - Post-meal rise in glucose levels is <3 mmol/L
- At next study visit, add rapid-acting insulin at other meals if glucose levels at other times of day consistently >10 mmol/L
  - Start rapid-acting insulin at 4 units or 10% of basal dose at other meals and titrate as below
  - Consider addition of correction insulin for hyperglycaemia if clinically appropriate

### For participants on basal bolus regimen

- In addition to the above monitoring, participants in the control group should also check their glucose levels two hours after meals (i.e., 2 hours after bolus insulin administered)
- If 2-hour post-meal glucose level is >3 mmol/L than pre-meal glucose level on 3 consecutive occasions then increase dose of rapid acting insulin by 2 units at applicable meal (i.e. can increase dose every 3 days if monitoring available)
- Stop uptitration of rapid acting insulin if any of the following occurs:
  - Glucose levels <4 mmol/L at any time of day
  - Post-meal rise in glucose levels is <3 mmol/L
- At next study visit, if glucose levels at other times of day consistently >10 mmol/L consider:
  - Increasing the dose of basal insulin as per above if glucose levels increase overnight
  - Adding rapid acting insulin with snacks
  - Adding correction insulin for hyerglycaemia

### For participants on once daily premixed insulin

- In addition to the above monitoring, participants in the control group should also check their glucose levels two hours after their largest meal (i.e., 2 hours after premixed insulin administered)
- If 2-hour post-meal glucose level is >3 mmol/L than pre-meal glucose level and fasting glucose level > 7 mmol/L on 3 consecutive occasions then increase dose of premixed insulin by 10% (i.e., can increase dose every 3 days if monitoring available)
- Stop uptitration of rapid acting insulin if any of the following occurs:
  - Glucose levels <4 mmol/L at any time of day
  - Post-meal rise in glucose levels is <3 mmol/L
  - Fasting glucose level < 7 mmol/L
- At next study visit, if glucose levels at other times of day consistently >10 mmol/L consider:
  - Adding bolus insulin at other meals and titrate as above
  - Changing premixed insulin analogue
  - Converting to twice daily premixed insulin and titrate as below

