## Methods

### Study design

This multi-centre, randomised controlled trial (RCT) of 80 participants will be conducted in Aotearoa New Zealand over a period of 14 weeks, including a 2-week run-in period for blinded CGM data to be collected from all participants. Following the 2-week run-in period, participants will be randomised 1:1 to either the rtCGM intervention arm (Dexcom G6 rtCGM system (Dexcom Inc., San Diego, CA)) or the control arm (SMBG) with a CareSens premier meter (i-SENS Inc., Seoul, Korea)) for a period of 12 weeks. The primary endpoint will be measured in the final two weeks of the RCT phase (week 10–12), with blinded rtCGM data collected from the control group and compared with unblinded rtCGM data from the intervention group. The 12-week RCT phase will be followed by a continuation phase, where those initially randomised to routine care will cross over into the rtCGM intervention for a further 12 weeks. Following this, participants will be invited to join the extension phase of this study and continue rtCGM use for a further 12 months. As such, the expected duration of subject participation is 78 weeks. At least five visits to the study centre and six ‘remote reviews’ are planned for participants over the study duration (see Table 1). During the 12-month extension phase participants will switch from using the Dexcom G6 system to the Dexcom G7 system, once available.

**Table 1 Tab1:** 2GO-CGM study schedule of assessments

	Baseline	Run-in period 14 days	Treatment period week 1–12				Continuation PERIOD Week 12–24			EXTENSION PERIOD Week 25–77			
	Clinic visit		Clinic visit day 1	Remote review week 2, 8	Week 10–12	Clinic visit end of study week 12	Clinic visit week 12	Remote review week 14, 20	Clinic visit end of study week 24	Week 38 remote review	Clinic visit week 51	Week 64 remote review	Clinic visit end of extension study week 77
Informed consent	X								X				
Demographics	X												
HbA1c Height, weight, BMI	X		X			X	X		X		X		X
Medical review	X					X	X		X		X		X
Blood pressure	X					X	X		X		X		X
Urine pregnancy test	X												
Fasting lipids, FBC, glucose, LFTS, eGFR	X					X	X		X		X		X
Urine ACR	X					X	X		X		X		X
Blinded CGM (14 days)		X			X (control arm)								
Return to clinic after 7 days of blinded CGM for new sensor		X			X (control arm)								
CGM training			X				X						
Electronic review				X				X		X		X	
AE collection		X	X	X		X	X	X	X	X	X	X	X
Sleep quality		X				X							
Food diary		X				X					X		

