### For participants on twice daily premixed insulin

- In addition to the above monitoring, participants in the control group should also check their glucose levels 2 hours after breakfast and dinner (i.e., 2 hours after premixed insulin administered)
- If 2-hour post-breakfast glucose level is >3 mmol/L than pre-breakfast glucose level and pre-dinner glucose level > 7 mmol/L on 3 consecutive occasions then increase dose of premixed insulin with breakfast by 10% (i.e., can increase dose every 3 days if monitoring available)
- If 2-hour post-dinner glucose level is >3 mmol/L than pre-dinner glucose level and fasting glucose level > 7 mmol/L on 3 consecutive occasions then increase dose of premixed insulin with dinner by 10% (i.e., can increase dose every 3 days if monitoring available)
- Stop uptitration of applicable premixed insulin if any of the following occurs:
  - Glucose levels <4 mmol/L at any time of day
  - Post-meal rise in glucose levels is <3 mmol/L
  - Pre-breakfast or pre-dinner glucose level < 7 mmol/L
- At next study visit, if glucose levels at other times of day consistently >10 mmol/L consider:
  - Adding bolus insulin at other meals and titrate as above
  - Changing premixed insulin analogue (s)

**NB:** Participants will be provided with individualised plans for self-titration of their insulin regimen. Adherence and safety of self-titration will be checked at each study visit. Clinical deviations from the protocol may be required e.g., starting at a lower dose of insulin if concerns over hypoglycaemia. Prandial insulin (either rapid-acting or premixed insulin as appropriate) will be encouraged at all meals where there is a consistent >3 mmol/L increase in glucose levels for 2–4 hours post meals. Non-insulin glucose lowering therapies will be continued throughout the study except for sulfonylureas, which will be stopped if prandial insulin is started at that meal. The initial insulins used in this study will be those prescribed by their normal health care providers and include:

- Basal insulins – glargine (Lantus®) and isophane (NPH; Protaphane®; Humulin® NPH)
- Rapid acting insulins – aspart (NovoRapid®), lispro (Humalog®) and glulisine (Apidra®)
  Premixed insulins – 30% aspart/70% isophane (NovoMix® 30), 25% lispro/75% isophane (Humalog Mix 25®) and 50% lispro/50% isophane (Humalog Mix 50®).

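### The stop rule for once-daily premixed insulin names the wrong insulin, so read literally a glucose below 4 mmol/L does not halt increases in the premixed dose

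*Protocol article*

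**What the plan says.** The appendix gives one titration section per insulin regimen. Each has a rule for increasing the dose and a list of findings that halt further increases.

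For once-daily premixed insulin, the increase needs a 2-hour post-meal rise above 3 mmol/L together with "fasting glucose level > 7 mmol/L on 3 consecutive occasions". The action is "then increase dose of premixed insulin by 10% (i.e., can increase dose every 3 days if monitoring available". The stop list is then introduced by "Stop uptitration of rapid acting insulin if any of the following occurs". Under it stand three criteria: "Glucose levels <4 mmol/L at any time of day", a post-meal rise under 3 mmol/L, and a fasting level under 7 mmol/L.

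The section for twice-daily premixed insulin introduces its list with "Stop uptitration of applicable premixed insulin if any of the following occurs".

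The section on glycaemic and cardiovascular risk management says that the prescribing nurses follow this appendix so that advice is standardised. The section on the randomised phase says that they give participants written titration instructions for use between scheduled reviews.

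**The concern.** The stop line names an insulin that the section does not titrate. The same line appears in the basal plus and basal bolus sections, where rapid acting insulin is the one being raised ("then increase dose of rapid acting insulin by 2 units" in basal plus), so the wording was apparently carried over.

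At stake is the hypoglycaemia stop. Participants adjust their own doses between reviews. Someone can meet the condition for an increase, with high fasting levels and a large rise after the main meal, and still go low at another time of day. The low-glucose criterion is the only printed rule that covers this case, and as worded it is not tied to the dose that is rising.

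**Working it through.** The point rests on comparing text. The protocol states no figure to reproduce.

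**Step 1. Compare the insulin increased with the insulin named in the stop line, for each appendix section.**

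| Regimen section | Insulin increased | Insulin named in stop line | Match |
|---|---|---|---|
| Basal only | basal | basal | yes |
| Basal plus | rapid acting | rapid acting | yes |
| Basal bolus | rapid acting | rapid acting | yes |
| Once-daily premixed | premixed | rapid acting | **no** |
| Twice-daily premixed | premixed | applicable premixed | yes |

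There is one mismatch in five sections. The term is not shorthand: the closing note of the appendix lists rapid acting and premixed insulins as separate classes with different products.

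**Step 2. Ask which stop criteria lose their effect on a literal reading.**

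- Post-meal rise under 3 mmol/L: an increase needs a rise above 3 on three consecutive occasions, so one smaller rise breaks the run.
- Fasting level under 7 mmol/L: an increase needs fasting above 7 on three consecutive occasions, so one lower value breaks the run.
- Glucose under 4 mmol/L at any hour: the increase condition says nothing about other times of day, so this criterion is independent of it.

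The first two still limit the dose whichever insulin is named. The third, 1 of 3, does not.

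**Step 3. Worked case (assumed values).** On three consecutive occasions: fasting 9.0, pre-meal 9.0 and 2-hour post-meal 13.0 mmol/L. One mid-afternoon reading: 3.6 mmol/L.

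- Increase rule: rise = 13.0 − 9.0 = 4.0 > 3, and fasting 9.0 > 7. It is met, so the dose goes up by 10%, for example 40 × 1.10 = 44 units.
- Stops: rise under 3, no; fasting under 7, no; glucose under 4, yes (3.6).

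Only the low-glucose criterion would hold the dose.

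**Step 4. Look for another safeguard in the printed rules.** The basal-only section sends converted participants on to the premixed sections without a premixed stop of its own. Its ceiling, "Doses of basal insulin reach 0.5 units/kg/day", applies to basal insulin. The once-daily premixed section has no ceiling. Neither do the other three sections, so this absence is not itself a sign of error; it only means that nothing stands in for the low-glucose stop.

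**Step 5. Bound the opportunity.** Table 1 (Study design) lists "Remote review week 2, 8" in the treatment period. The longest gap between scheduled reviews is (8 − 2) × 7 = 42 days, and 42 / 3 = 14 possible three-day titration points. This is an upper limit on opportunities, not an expected number of increases: each increase needs its condition met on three consecutive occasions, and the stop matters only if a low also occurs.

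**The case against.** The strongest reply is that only one reading makes sense. The section is headed for premixed insulin and, before the stop line, raises nothing else. Its fasting criterion is absent from the rapid acting lists and mirrors the premixed increase condition. Rapid acting insulin enters only later, as an option at the next visit, to be titrated under the earlier sections. The users are prescribing specialist nurses with endocrinologist support, who write individualised plans, may deviate over hypoglycaemia concerns, and check the safety of self-titration at study visits. Participants using real-time CGM can also set low-glucose alerts. For harm to follow, a prescriber would have to leave out a stop that every other section attaches to the titrated insulin.

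Most of this stands, and it keeps the point small. It does not make the line correct. The section itself offers bolus insulin at other meals. For a participant who takes that step, the literal text becomes workable but wrong: after a low, hold the bolus and continue to raise the premixed dose. A document meant to standardise dosing advice should not leave its hypoglycaemia stop to inference. The algorithm is credited to a national guideline that is not at hand, so the slip may come from that source, but the text to correct is the same.

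**Conclusion.** The concern holds. The once-daily premixed section names the wrong insulin in its stop line and, on the literal wording, the low-glucose criterion does not govern the dose being increased. It is a minor safety-wording error: 1 of 3 stop criteria, in 1 of 5 regimen sections, for a number of participants that the protocol does not give. The 14 titration points are a ceiling for the longest review gap in the randomised phase. The conclusion depends on reading the line as printed; prescribers will probably apply the intended meaning. Sample size, type 1 error control and the primary analysis are untouched.

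**What to change.** In the stop line of the once-daily premixed section, replace the reference to rapid acting insulin with premixed insulin, in line with the twice-daily section. Then check that written self-titration plans already given to once-daily premixed users state that a reading under 4 mmol/L halts increases in the premixed dose, and reissue any that do not. The cost is one term in the appendix and a short check of issued plans, with no extra data and no change to the analysis.

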### For participants on twice daily premixed insulin

- In addition to the above monitoring, participants in the control group should also check their glucose levels 2 hours after breakfast and dinner (i.e., 2 hours after premixed insulin administered)
- If 2-hour post-breakfast glucose level is >3 mmol/L than pre-breakfast glucose level and pre-dinner glucose level > 7 mmol/L on 3 consecutive occasions then increase dose of premixed insulin with breakfast by 10% (i.e., can increase dose every 3 days if monitoring available)
- If 2-hour post-dinner glucose level is >3 mmol/L than pre-dinner glucose level and fasting glucose level > 7 mmol/L on 3 consecutive occasions then increase dose of premixed insulin with dinner by 10% (i.e., can increase dose every 3 days if monitoring available)
- Stop uptitration of applicable premixed insulin if any of the following occurs:
  - Glucose levels <4 mmol/L at any time of day
  - Post-meal rise in glucose levels is <3 mmol/L
  - Pre-breakfast or pre-dinner glucose level < 7 mmol/L
- At next study visit, if glucose levels at other times of day consistently >10 mmol/L consider:
  - Adding bolus insulin at other meals and titrate as above
  - Changing premixed insulin analogue (s)

**NB:** Participants will be provided with individualised plans for self-titration of their insulin regimen. Adherence and safety of self-titration will be checked at each study visit. Clinical deviations from the protocol may be required e.g., starting at a lower dose of insulin if concerns over hypoglycaemia. Prandial insulin (either rapid-acting or premixed insulin as appropriate) will be encouraged at all meals where there is a consistent >3 mmol/L increase in glucose levels for 2–4 hours post meals. Non-insulin glucose lowering therapies will be continued throughout the study except for sulfonylureas, which will be stopped if prandial insulin is started at that meal. The initial insulins used in this study will be those prescribed by their normal health care providers and include:

- Basal insulins – glargine (Lantus®) and isophane (NPH; Protaphane®; Humulin® NPH)
- Rapid acting insulins – aspart (NovoRapid®), lispro (Humalog®) and glulisine (Apidra®)
  Premixed insulins – 30% aspart/70% isophane (NovoMix® 30), 25% lispro/75% isophane (Humalog Mix 25®) and 50% lispro/50% isophane (Humalog Mix 50®).
